## Abstract

**Background:**

Because of the lack of anesthesia workforce, anesthesiologists are forced to work overtime and more night shifts, which can disturb their biological rhythm and cause severe stress and depression, potentially leading to negative and even devastating outcomes for both themselves and patients. Virtual reality (VR), a new method to reduce stress and pain for patients, has been widely used in biomedical fields. The purpose of this study is to evaluate the potential effectiveness of VR technology in reducing stress among night-shift anesthesiologists.

**Methods:**

In this randomized controlled, crossover, single-center clinical trial, a total of 30 anesthesiologists will be enrolled and randomized in a 1:1 allocation to either the VR immersion group (intervention group) or the routine night-shift group (control group) with a washout of 1 week. Anesthesiologists in the intervention group will undergo VR immersion twice, while anesthesiologists in the control group will not watch VR videos during the night shift. The primary outcome will be the difference in the NASA Task Load Index (NASA-TLX) score between the two groups. Secondary outcomes will include the Chinese Perceived Stress Scale (CPSS), perceived stress scores (visual analogue scale (VAS)), and Multidimensional Fatigue Inventory (MFI-20) scores; levels of satisfaction among the participants; incidence of arrhythmia; and incidence of chest tightness, headache, and palpitations.

**Discussion:**

It is unknown whether the use of VR technology during the night shift can reduce stress among anesthesiologists. With the widespread use of VR technology, a positive result in this trial could spur hospitals to apply VR technology to reduce stress among night-shift doctors in every department and provide a relatively relaxed working environment.

**Trial registration:**

Chinese Clinical Trial Registry ChiCTR2000031025. Registered on 21 March 2020

## Background

More than 300 million people need to undergo surgery each year worldwide [1]; more than 70% of those people have no access to safe, affordable anesthesia or surgical care [2], and the severe lack of anesthesiologists is one of the causes of this phenomenon [3]. The lack of first-line doctors also leads to more work overload and night shifts, which disturbs the biological rhythm and causes severe stress and depression [4, 5]. Due to long working hours, work overload, chronic sleep deprivation, the need for sustained vigilance, continuous noise pollution and even halitosis among patients [6], and the risk of COVID-19 [7], anesthesiologists face high levels of job-related stress [8, 9], which causes anxiety, depression, sleep disturbances, memory and attention problems, nightmares, the need for medication, and so on [10, 11]. Lindfors et al. [12] showed that approximately 68% of Finnish anesthesiologists felt stress at work, and the proportion was 79% in Ireland [13]. It has been reported that anesthesiologists suffer higher levels of anxiety and stress than those in other occupations [14]. When anesthesiologists are under high levels of stress for a long time, there may be negative or even devastating outcomes for the patients. Therefore, an intervention that could reduce stress among night-shift anesthesiologists could be valuable in enhancing medical safety and protecting the health of the anesthesiologists.

Recently, virtual reality (VR) has been widely used in biomedical fields [15]. It can alter our sense of personal presence to that of being in a virtual world; therefore, the features of sensory and affective experience can be changed. This new technology has been applied in hospitals to create an immersive environment to minimize stress for both patients and healthcare providers [16–18]. For instance, VR has been widely used before surgery to reduce preoperative anxiety (measured using visual analogue scales (VAS)) in patients [19]. Moreover, the broad reach of VR has enabled its use for treating pain, psychological stress, social and generalized anxiety disorders, depression, and posttraumatic stress disorder (PTSD) as well as helping with poststroke rehabilitation [20]. In addition, VR technology had been used by surgeons in clinical work to decrease the physical and mental workload [21] and reduce the stress response and cognitive load in inpatient oncology nurses [16]. However, few studies have focused on the application of VR technology to reduce stress among night-shift anesthesiologists. Therefore, we conducted this study to investigate the potential effectiveness of VR technology in reducing stress among night-shift anesthesiologists.

## Methods/design

### Study design

The virtual reality immersion in the night-shift anesthesiologist trial is a randomized controlled, single-center clinical trial using a crossover design with a washout of 1 week. Anesthesiologists will be randomized in a 1:1 allocation to a sequence of either immersion relaxation using VR in the first period, followed by no immersion VR in the second treatment period, or no immersion VR in the first period, followed by immersion relaxation using VR in the second period. Anesthesiologists undergoing VR intervention will undergo immersion relaxation via VR twice during the night shift: the first session will occur at 23:30, and the second session will occur at 07:30 the next day. The anesthesiologists will be able to choose VR content and enjoy themselves for 20 min. Anesthesiologists in the control group will not watch VR videos during the night shift. The design of the study is presented in Fig. 1.

**Fig. 1 Fig1:**
[figure not shown]
The crossover design of the study

The primary outcome of the study will be the NASA Task Load Index (NASA-TLX) at 07:50 of the next day, which consists of six dimensions rated on a 100-point scale in each dimension (physical demand, mental demand, temporal demand, effort, performance, and frustration) and is widely used to measure the mental workload [22, 23]. Secondary outcomes will be the Chinese Perceived Stress Scale (CPSS), perceived stress scores (visual analogue scale (VAS)), and Multidimensional Fatigue Inventory (MFI-20) scores; the level of satisfaction among participants; heart rate (HR); blood pressure (BP); and incidence of arrhythmia, chest tightness, headache, and palpitations at all the recorded timepoints. The CPSS was used to assess the severity of participants’ psychological stress as earlier reported [24]. Perceived stress score was assessed via the VAS score, which was defined as the length in millimeters from 0 (no stress) to 10 (unbearable stress) [25]. The MFI-20 score was used to quantify the impact of fatigue [26], including five independent subscales of fatigue: general fatigue, mental fatigue, physical fatigue, reduced activity, and reduced motivation.

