### Data collection

The participants’ general characteristics, including sex, age, body mass index (BMI), heart rate (HR), blood pressure (BP), and electrocardiogram (ECG) data, will be collected. To assess the effect of VR immersion on stress among night-shift anesthesiologists, data will be collected from participants in the intervention group at six timepoints: baseline status (07:50 am, T1), initiation of night shift (17:30, T2), before first VR immersion (23:30, T3), after first VR immersion (23:50, T4) on the day that they work the night shift and before second VR immersion (07:30, T5), and after first VR immersion (07:50, T6) of the next day. At each timepoint, participants will be asked to measure their stress status via completing the scales which included NASA-TLX, CPSS, VAS, and MFI-20. In addition, ECG will be measured using a mobile ECG recorder (CardioLearn; HeartVoice Medical Technology Co., Ltd., Anhui, China) at each timepoint following the manufacturer’s instructions. The mobile device has been widely used in China to simply measure the ECGs and automatically analyze their results based on a novel deep learning-based cloud service as earlier reported [27, 28]. Furthermore, the anesthesiologists will be invited to record their ECG whenever they feel discomfort during the night shift. The incidence of arrhythmia, level of satisfaction, and incidence of chest distress, headache, or heart palpitations will also be recorded by the researchers. The data recording flow chart is presented in Fig. 2 and the SPIRIT figure is shown in Fig. 3.

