### Reporting of compliance and adverse events

To avoid possible bias, participants who had experienced something very pleasant or sad during the washout time will be asked to report their own emotion status before the second enrollment. This would be recorded and judged by two independent psychologists and those who get married or promoted, whose child is born, or whose family member is dead would be excluded from the final analysis. It has been reported that young people are more vulnerable to physical discomfort, such as seizures, severe dizziness, eye twitching, or blackouts triggered by light flashes when wearing a VR headset [29]; therefore, for participants who experience any discomfort during the VR immersion procedure, the trial can be stopped, and the participants will be treated accordingly. All these events are recorded and reported. To ensure the safety of patients, anesthesiologists with the same qualifications will take over the participants’ work during the VR immersion.

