#### Analysis of the secondary outcomes

The effect of VR immersion on the CPSS, VAS, and MFI-20 scores will be compared using one-way analysis of variance for the 2 × 2 crossover design. Spearman’s rank correlation test will be used to analyze the association between work hours and scores on the scales. The age, BMI, HR, MBP, and the level of satisfaction between groups will be analyzed by the Student *t* test or the Wilcoxon rank-sum test. The gender, incidence of arrhythmia, chest distress, headache, and heart palpitations between groups will be analyzed by the Pearson *χ*^2^ test or Fisher’s exact test.

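### The headset reactions the protocol names are recorded only during immersion and are not in the symptom list compared between nights, so later or control-night dizziness has no stated record

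*Protocol article*

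**What the plan says.** The outcome text under Study design lists, among the secondary outcomes, "incidence of arrhythmia, chest tightness, headache, and palpitations at all the recorded timepoints". Data collection repeats the list: arrhythmia is recorded, and the "incidence of chest distress, headache, or heart palpitations will also be recorded by the researchers". Analysis of the secondary outcomes then tests the "incidence of arrhythmia, chest distress, headache, and heart palpitations between groups" by the Pearson chi-square or Fisher's exact test. The Abstract gives the same four items.

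The section Reporting of compliance and adverse events describes the headset's own risks: younger people are said to be more prone to "physical discomfort, such as seizures, severe dizziness, eye twitching, or blackouts triggered by light flashes when wearing a VR headset". It continues that "for participants who experience any discomfort during the VR immersion procedure, the trial can be stopped, and the participants will be treated accordingly", and closes with "All these events are recorded and reported". Inclusion and exclusion criteria uses the same four reactions to keep out people who have already had them with a headset.

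Two further statements bear on the point. Data collection invites participants to take an ECG whenever they feel unwell during the night shift. Data analysis restricts the analysis to participants who complete the study according to the intervention plan.

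**The concern.** The protocol identifies what the headset may do to the wearer, but the symptoms it compares between the VR night and the control night contain none of those reactions. The route that does capture them is tied to the immersion itself. A participant who becomes dizzy after returning to work falls outside that window and outside the symptom list. Dizziness on the control night, for example from fatigue, falls outside both as well, so VR-night dizziness cannot be set against a background rate.

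The Discussion says that a positive result could spur hospitals to offer VR to night-shift doctors in every department. For that use, dizziness in a doctor who has just returned to patient care is relevant. A report that the listed symptoms did not differ would say nothing about it.

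**Working it through.** **1. The lists side by side.** Chest tightness and chest distress are treated as one item.

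| Item | Outcome list (Study design) | Recorded (Data collection) | Tested (Analysis of the secondary outcomes) | Named headset reaction |
|---|---|---|---|---|
| Arrhythmia | yes | yes | yes | no |
| Chest tightness/distress | yes | yes | yes | no |
| Headache | yes | yes | yes | no |
| Palpitations | yes | yes | yes | no |
| Severe dizziness | no | no | no | yes |
| Eye twitching | no | no | no | yes |
| Blackout | no | no | no | yes |
| Seizure | no | no | no | yes |

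The overlap is 0 of 4.

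**2. The time covered by the adverse-event route.** The shift runs from 17:30 to 08:00 (Setting), which is 14 h 30 min = 870 min. Immersion is 2 × 20 = 40 min (Study design), or 40/870 = 4.6% of the VR-night shift. It is 0 min of the control-night shift. Time on duty after an exposure on the VR night is 23:50 to 07:30 = 460 min, plus 07:50 to 08:00 = 10 min, in total 470 min. In those 470 min the only stated contact for feeling unwell is the invited ECG, whose output is a tracing and not a symptom record.

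**3. What the added items could show.** The protocol gives no figure for this comparison. The only inputs from it are 26 evaluable and 30 recruited participants (Sample size estimation). The step from 26 to 30 checks: 26/0.9 = 28.9, rounded up to 29, then to 30 for equal sequences.

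- *Smallest significant result with no control-night events.* For Fisher's exact test, 5 against 0 gives p = 0.051 (n = 26) or 0.052 (n = 30), and 6 against 0 gives p = 0.023 or 0.024. Both nights come from the same person, so the exact McNemar test, p = 2 × 0.5^x, is also shown: x = 5 gives 0.0625 and x = 6 gives 0.031. Six events are needed either way.
- *Chance of six or more events.* This is the binomial tail P(X ≥ 6) with n = 26 or 30. The VR-night rates are assumptions, because the protocol gives none.

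| Assumed rate | n = 26 | n = 30 |
|---|---|---|
| 2% | 0.001% | 0.003% |
| 5% | 0.15% | 0.33% |
| 10% | 4.0% | 7.3% |
| 20% | 42% | 57% |

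- *Chance of seeing at least one event*, 1 − (1 − p)^n: at 5%, 74% (n = 26) or 79% (n = 30); at 10%, 94% or 96%.
- *If no event is seen*, the one-sided 95% upper limit is 1 − 0.05^(1/n): 10.9% (n = 26) or 9.5% (n = 30).

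A formal test would therefore rarely reach significance unless the reaction were common. A count with an upper limit is informative, provided that the question is asked.

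**4. The analysis set.** A participant whose session is stopped for a reaction may not count as completing according to the intervention plan. That person could then drop out of the compared data, including the four listed symptoms. The protocol does not say how such a participant is classified, so this is a possibility and not a certainty.

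**The case against.** The strongest case is that nothing here is misstated. Adverse events have their own section, and it promises that reactions during immersion are recorded and reported. A reader might infer that the named reactions are not collected at all; the text does not support that.

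A reader might also infer that a designated safety comparison has been built so that it cannot show the harm VR is expected to cause. That goes too far as well. No section calls the four compared symptoms safety items. They stand beside the stress and fatigue scales and read most naturally as stress outcomes, and headache could in principle reflect the headset too. Reactions triggered by light flashes in a headset cannot occur on a control night, so a VR-night count shows those directly without a comparator. The entry exclusion also lowers the expected rate, although it cannot screen out people who have never worn a headset.

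Other points stand in part. The protocol does not say how reactions are elicited, so it cannot be assumed that they are left to spontaneous report. After the second session only 10 minutes of the shift remain, so the long gap concerns the first session only. The case report form, the recording flow chart and the SPIRIT figure are not visible and may hold a longer checklist. Against this, the article gives the same symptom list in four places and separately fixes when headset reactions are captured.

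What remains is narrow: dizziness, a non-specific symptom, has no stated record after the headset comes off or on the control night.

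**Conclusion.** The point holds as a cheap improvement of minor severity. None of the 4 named headset reactions is among the 4 symptoms compared between nights. The stated route for them covers 40 of 870 minutes on the VR night and none of the control night. The practical loss is mainly dizziness during the 460 minutes after the first session, together with its background rate on the control night.

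This rests on three assumptions: that the symptom list in the article is complete; that the control night uses the same timepoints, which Data collection spells out only for the VR night but which a between-night comparison presupposes; and that dizziness on a long night shift can have causes other than the headset. No event rate can be taken from the protocol, so the number of reactions that would go unseen cannot be estimated.

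**What to change.** Add severe dizziness, eye twitching, blackout and seizure as yes/no items to the symptom record at the existing timepoints, on both the VR and the control night. Word each item to cover the time since the previous timepoint, so that the 07:30 record reaches back to 23:50. Name the four items in the outcome list under Study design, in Data collection and in Analysis of the secondary outcomes.

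Report them as descriptive counts by night for everyone exposed to VR, including participants stopped early and therefore possibly outside the per-protocol set. Where no event occurs, give the upper confidence limit. Leave the stopping and treatment wording in Reporting of compliance and adverse events unchanged: the change concerns what is recorded, not when a participant is stopped or treated.

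The cost is four tick-boxes, a few more seconds per assessment and some sparse rows in the results table. The sample size does not change.

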### Setting

The study will be conducted in the Third Affiliated Hospital of Sun Yat-sen University, a large comprehensive hospital in Guangzhou, China. The hospital is a tertiary medical facility that serves as a teaching hospital for Sun Yat-sen University, including 65 anesthesiologists in the Department of Anesthesiology, and the age of the front-line clinicians is 25 to 45. Besides, each anesthesiologist only undergoes one night shift each arm and works from 17:30 to 8:00 of the next day.

### Ethical approval and registration

The study protocol will be carried out in accordance with the principles of the Declaration of Helsinki, approved by the Institutional Review Board (IRB) of the hospital (approval number: [2020] 02-021-01), and registered with the Chinese Clinical Trial Registry at www.chictr.org on 21 March 2020 (registration no. ChiCTR2000031025). All the items of the WHO Trial Registration Data Set (TRDS) can be found in the protocol. The trial is currently active and ongoing, and any amendments to the protocol can be reported to and approved by the IRB. The participants can voluntarily withdraw from the study after providing informed consent.

### Inclusion and exclusion criteria

To be eligible, participants must meet all of the following inclusion criteria: (1) participants who work for the hospital, (2) aged 25–45 years, (3) the patients they are managing are class I or class II according to the American Society of Anesthesiologists (ASA), and (4) each operation takes 2 to 4 h. The exclusion criteria are as follows: (1) participants who refuse to sign the informed consent form, (2) participants with serious cardiopulmonary diseases, and (3) participants who had experienced physical discomfort, such as seizures, severe dizziness, eye twitching, or blackouts triggered by light flashes when they wore a VR headset.

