### Randomization

Following informed consent, participants will be randomized in a 1:1 allocation to a sequence of either immersion relaxation using VR in the first period, followed by no immersion VR in the second treatment period, or no immersion VR in the first period, followed by immersion relaxation using VR in the second period, based on a computer-generated random number that is concealed via a sealed envelope. One of the researchers conducts this step. The allocation will not be disclosed to the other researchers who conduct the trial until the participant is enrolled and assigned. In addition, researchers who perform the statistical analyses will be blinded to the group allocation.

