### Intervention group: virtual reality immersive relaxation

Participants in the VR immersion group (intervention group) will be asked to wear the VR headset (Pico G2 4K; Pico Technology Co., Ltd.; China) and choose the 360-degree panoramic videos on natural scenery around the world at https://vr.iqiyi.com/ based on their preferences to relax themselves in the resting room. In order to avoid selection bias stemming from the content of the videos, such as terrifying videos or rock songs, which may influence relaxation, the content of videos is limited to natural scenery. Considering the limitation of resting time in clinical practices, participants experience VR immersion for only 20 min for each time and they will be asked to watch videos for 20 min at 23:30 and at 07:30 of the next day. The timepoints are chosen based on our preliminary data that most first-line anesthesiologists would feel stress and overworked after 23:00, and the handover time of the night shifts (08:00 of the next day). In addition, according to our preliminary study, it took about 5 min to complete all the assessments at each timepoint. Thus, the participants are asked to complete the NASA-TLX, CPSS, VAS, and MFI-20 5 min before the specified timepoint. When the participants are watching the videos, anesthesiologists with the same qualifications will take over their work until the VR immersion is complete.

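### The only VR-safety exclusion depends on a past reaction to a headset, so a headset-naive anesthesiologist with known light-triggered seizures or blackouts is eligible and scheduled for two VR sessions

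*Protocol article*

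**What the plan says.** The section Inclusion and exclusion criteria of the protocol article gives three exclusions. The first two are "1) participants who refuse to sign the informed consent form, (2) participants with serious cardiopulmonary diseases". The third is "participants who had experienced physical discomfort, such as seizures, severe dizziness, eye twitching, or blackouts triggered by light flashes when they wore a VR headset". The inclusion criteria that describe the participant are "1) participants who work for the hospital, (2) aged 25–45 years"; the other two concern the ASA class of the patients being managed and the length of the operations.

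The section Reporting of compliance and adverse events cites a report that "young people are more vulnerable to physical discomfort" of the same kinds when wearing a headset. It then provides that "for participants who experience any discomfort during the VR immersion procedure, the trial can be stopped" and that the participant will be treated.

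On exposure, the intervention section says of the VR night that "they will be asked to watch videos for 20 min at 23:30 and at 07:30 of the next day". Under Setting, "each anesthesiologist only undergoes one night shift each arm and works from 17:30 to 8:00 of the next day". Under Randomization, one sequence has VR first, and the other is "no immersion VR in the first period, followed by immersion relaxation using VR in the second period". An equally qualified colleague covers the participant's work while the headset is on; this is stated in the intervention section, in the adverse-events section and among the limitations in the Discussion.

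**The concern.** The third criterion is evidently there to keep people prone to these reactions out of a headset. Its trigger, however, is an earlier headset reaction and not the susceptibility itself. Someone who knows from another source of light that they have seizures or blackouts, and who has never worn a headset, passes screening as written. The first test of that person's susceptibility would then be the trial exposure.

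What is at stake is mainly participant safety. There is a narrower issue for patients: the participant is due back at work after the first session, and the article states no cover beyond the session. For the trial's answer, a person stopped because of a VR reaction would not have completed the plan. The Data analysis section limits the analysis to completers, so that person would drop out of it. Such losses can arise only on VR nights, although few would be expected.

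**Working it through.** No figure in the article bears on this point, so the check is a reading of the sections side by side, with simple arithmetic on the schedule.

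**1. Apply the eligibility list to a test case.** Take a hospital anesthesiologist aged 27 with known light-triggered seizures, no headset history, and qualifying patients and operations.

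| Criterion | Result |
|---|---|
| Inclusion: hospital staff, aged 25–45 | met |
| Inclusion: patients' ASA class, operation length | met by assumption; says nothing about the participant's history |
| Exclusion 1: refuses consent | not met if the person consents |
| Exclusion 2: serious cardiopulmonary disease | not met |
| Exclusion 3: past reaction while wearing a headset | not met; no headset has been worn |

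The person is eligible. The same person with an earlier headset reaction would be excluded. One who had tried a headset without reacting would not be, so the criterion turns on a past reaction and not on past use alone.

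**2. Try the other reading of criterion 3.** Suppose it means reactions to the trial's own headset. It then screens nobody before exposure and becomes an exclusion after randomization, because no headset session before randomization is described. Neither reading identifies the test case in advance.

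**3. Planned exposure.** Both sequences contain a VR night, so every participant is scheduled for 2 sessions of 20 minutes, or 30 × 2 = 60 sessions in all. Two is the planned number; a reaction in the first session could lead to the second being stopped.

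**4. Timing within the shift.** The shift runs from 17:30 to 08:00, which is 14.5 h.
- Session 1: 23:30 to 23:50. It starts 6 h into the shift and leaves 8 h 10 min afterwards.
- Session 2: 07:30 to 07:50. It starts 14 h into the shift and leaves 10 min afterwards.

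Session 1 is therefore mid-shift and session 2 is at its end. The cover arrangement is tied to the VR session, so any period without stated cover matters mainly after 23:50.

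**5. Set the risk statement beside the criterion.** The adverse-events section names the same reactions and the same condition (headset use) and says younger people are more prone. The measure it draws from this is reactive: stop and treat. The eligibility section is the only place where anything is done beforehand, and step 1 shows whom it misses.

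**6. Room in the sample size.** Taking the article's requirement of 26 as given, the plan recruits 30, a margin of 4. Losing a participant or two to a VR reaction stays within that margin. The department has 65 anesthesiologists, 65 − 30 = 35 more than are needed.

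**The case against.** Several points on the other side have force.

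- **The two sections do not contradict each other.** Both speak of reactions while wearing a headset, and the adverse-events section moves from the risk to stopping and treating, not to screening. A reader might infer an outright inconsistency; the text does not support that. What stands is that the criterion is aimed at a named harm and misses a foreseeable case.
- **An article condenses.** A fuller protocol or the consent material may ask about seizure history, so one cannot conclude that nobody is asked. But the article prints the exclusion criteria as a definite list, and the weakness lies in the wording of a printed criterion, not in a missing detail.
- **Patients are covered during VR.** A reader might infer that anesthetized patients are left with someone having a reaction. The article says otherwise: a colleague has the work for the whole session, which is when a light-triggered event is most likely. Only the time after the session is unaddressed.
- **Other mitigations exist.** Content is limited to natural scenery, sessions last 20 minutes, and participants are physicians who consent and may withdraw. These may lower the risk. The content limit, however, is justified by its effect on relaxation and not by light sensitivity, and self-exclusion is not a screening rule.
- **The numbers are likely tiny.** A reader might count every headset-naive participant as at risk. That would be wrong: it counts people on whom the criterion is silent, not people who are susceptible. The article gives neither figure.

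**Conclusion.** The point holds as a defect in a stated criterion. As written, criterion 3 admits a headset-naive person with known light-triggered seizures or blackouts, and the crossover schedules that person for two VR sessions. The protocol itself treats such reactions as foreseeable with headset use, yet describes no step before randomization that would pick up this history.

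Its size cannot be estimated from the article, which gives neither the frequency of such a history among staff nor the share who have worn a headset. Among practising anesthesiologists it is probably very small. The case rests on how serious and foreseeable the harm is and how little the change costs, not on frequency. A reader might infer a meaningful bias in the NASA-TLX comparison or a threat to power. The documents do not support that: the margin of 4 over the stated requirement would absorb one or two losses.

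The conclusion assumes that the printed list is the operative one and that no screening question in an unseen document already covers this history. How far the 25–45 age range falls under the article's remark about young people is not defined, and the conclusion does not depend on it.

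**What to change.** Reconcile the eligibility section with the adverse-events section. Reword criterion 3 so that it does not depend on earlier headset use and covers known susceptibility to the reactions the protocol already lists, ascertained by a question at screening, before randomization. The exact clinical wording and threshold are for the sponsor and the IRB. The article says the trial is ongoing and that amendments can be reported to and approved by the IRB, so a route exists. In the same amendment, state whether colleague cover continues after a session in which a participant has reacted.

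The cost is one amended criterion and one screening question, with no added procedure. The downside is possibly slightly fewer eligible staff, from a department of 65 with 30 needed, and results that apply to people without such a history.
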